**Figure 2 F2:**
[figure not shown]
**Simplified version of the treatment scheme for heart failure.** HF-REF = heart failure with reduced ejection fraction, HF-PEF = heart failure with preserved ejection fraction, EF = ejection fraction, ACE = angiotensin converting enzyme, ARB = angiotensin receptor blocker, min = minute, RR = blood pressure, ECG = electrocardiogram, AV-block = atrioventricular block.

The GPs randomly allocated to the control group will manage patients with a newly screen-detected diagnosis of HF as they are used to (care as usual). They are expected to follow the same Dutch heart failure guideline, however, they will lack the guided up-titration scheme and will not receive a special training.

Referral to a cardiologist is possible at any stage in this pragmatic trial. GPs in both groups will receive instructions about when it is advisable to refer patients for specialist consultation in line with the guidelines on HF, e.g. if patients remain symptomatic after the up-titration phase, in case of complications or adverse effects, and when a novel treatable cause of HF is suspected.

The E/e’ ratio is regarded as a key parameter for assessing diastolic dysfunction; an E/e’ greater than or equal to 15 is considered abnormal, an E/e’ value between 9 and 14 indeterminate, and an E/e’ less than 9 as normal. In case the E/e’ is indeterminate, at least two additional abnormal parameters are needed to establish diastolic dysfunction [20,23]; an E/A ratio below 0.75 or above 1.5, an E-deceleration time >280 ms, a time difference between the duration of the atrial reversal velocity and the late diastolic mitral inflow duration (Ar - A) of more than 30 ms, a left atrial volume index > 34 ml/m^2^, a left ventricular mass indexed by body surface area > 95 g/m^2^ in women, and > 115 g/m^2^ in men (according to the formula of Devereux [24].

A complete assessment of diastolic dysfunction is not possible in participants with atrial fibrillation. In such participants an elevated indexed left atrial volume (≥34 ml/m^2^) in combination with AF will be considered sufficient to establish diastolic dysfunction.

To diagnose isolated right-sided HF, patients need to have signs and symptoms of HF in combination with a LVEF > 45%, and an increased pulmonary artery pressure (calculated systolic pulmonary artery pressure >40 mmHg), in the absence of (overt) diastolic dysfunction.

By re-assessment of a random sample of 10% by the same outcome panel, blinded to the original decision, the reproducibility of the panel diagnoses will be evaluated.

#### Functional capacity

For the elderly HF patient exercise intolerance can be very limiting and of major clinical importance. We chose the 6MWT for the objective evaluation of submaximal functional capacity in patients with newly established HF, because the exercise level is consistent with daily physical activities [21]. The 6MWT is considered a valid, easy, well-tolerated, and inexpensive test [25] that measures the distance that a patient can walk on a flat, hard surface during 6 minutes. The test will be executed according to the guidelines of the American Thoracic Society [21].

#### Health-related quality of life

The SF-36 [26,27] and EQ-5D [28,29] were chosen as instruments to measure general health status of all participants. In addition, the scores of the EQ-5D will be converted to a time trade-off utility score to calculate quality-adjusted life years for the cost-effectiveness analysis.

The MLHF questionnaire was added as a condition-specific measurement for HF patients to evaluate the patients’ perception of the effects of HF on the physical, socioeconomic and psychological aspects of their life. All questionnaires are well validated and widely used.

#### Costs

Relevant cost parameters within and outside the healthcare system will be collected prospectively during a follow-up period of 12 months. Direct costs within the health care system will be monitored through the electronic medical patients files of the GPs, including the costs of further diagnostic testing, time consumption of health care workers (i.e. GP contacts, referrals to medical specialists, hospital admissions), and treatment expenses. Costs outside the healthcare system include the estimation of time-investment and travelling expenses patients make. As the population under study is older than 65 years of age, costs of productivity loss will not be studied. Regarding the standardization of costs, we will use a uniform costing methodology [30].

### Statistical analyses

Prevalence rates of newly established HF-REF, HF-PEF and isolated right sided HF in our population with shortness of breath on exertion will be calculated as proportions with 95% confidence intervals.

Differences in functionality and quality of life after 6 months of follow-up, and uptake of HF medication between both groups after 6 and 12 months of follow-up will be compared taking into account potential difference of relevant parameters at baseline (ANCOVA), although such differences are expected to be minimal because of the randomization procedure. This will be done separately for patients with HF-REF and HF-PEF. A multilevel approach is used in the analyses to correct for the fact that we randomized at the level of the GP and not at the patient level.

The cost-effectiveness of training GPs in the management of HF and the practical application of an up-titration scheme will be evaluated and compared with care as usual. Cost-effectiveness will be expressed in terms of costs per quality-adjusted life year gained (cost-utility analysis). Estimates have to be made in the calculation of the costs and the definition of effects, and these are subjected to different margins of uncertainty. To assess to what extent the results of the analysis depend on prior assumptions and choices made, a sensitivity analysis will be performed conform current Dutch standards for pharmacoeconomic research [31].

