### Sample size

The difference in mean distance walked during the six-minute walking test (6MWT) between the two groups after six months follow-up will be taken as the primary outcome. The average distance walked by HF patients ranges from 242 m (standard deviation 71 m) up to 427 m (standard deviation 100 m), depending on the severity of HF [13]. Since it was shown that an increase of 50 m in walking distance indicated a clinically relevant change [14,15], we consider a mean difference of 50 meters between groups as the minimal important difference to show an effect of the intervention.

We used the two-sample t-test power analysis to examine how many HF patients are needed per group to demonstrate an effect. With an effect size of 0.6, alpha of 0.05, and beta of 0.2, group sample sizes of two times 45 will be sufficient.

We assume that in a standard general practice with 2400 patients, at least 50 patients aged 65 years or over will experience shortness of breath during a one-year period. The prevalence of previously unrecognized HF in such patients is expected to be around 14% (10.4-17.5%) [16]. With a participation rate of 50%, a mean number of 3.5 patients per GP are expected to have newly detected HF (50% HF-REF and 50% HF-PEF). Twenty-six general practitioners are needed to reach the targeted number of HF patients. We will include 4 extra practices to allow for taking clustering into account.

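### The trial is sized for one comparison in all heart failure patients, but the stated analysis compares the arms only within HF-REF and HF-PEF, where power is about 50% on the plan's own basis

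*Protocol article*

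**What the plan says.** Under Sample size, the protocol article defines its primary outcome as one comparison with no restriction by subtype: "The difference in mean distance walked during the six-minute walking test (6MWT) between the two groups after six months follow-up will be taken as the" (the quote breaks off just before the outcome is labelled as primary). The power method is also for heart failure patients as a whole: "We used the two-sample t-test power analysis to examine how many HF patients are needed per group to demonstrate an effect". The result is: "With an effect size of 0.6, alpha of 0.05, and beta of 0.2, group sample sizes of two times 45 will be sufficient". The target difference is 50 m: "we consider a mean difference of 50 meters between groups as the minimal important difference to show an effect of the intervention".

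The number of practices is derived by counting both subtypes together: "a mean number of 3.5 patients per GP are expected to have newly detected HF (50% HF-REF and 50% HF-PEF"), followed by "Twenty-six general practitioners are needed to reach the targeted number of HF patients". Four further practices are added for clustering, which makes 30.

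Under Statistical analyses, functionality and quality of life at 6 months, and medication uptake at 6 and 12 months, are to be compared between arms by ANCOVA with a multilevel approach. The next sentence is: "This will be done separately for patients with HF-REF and HF-PEF". The section mentions no comparison across subtypes.

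**The concern.** The two sections describe different primary comparisons. Sample size treats all heart failure patients as one population, and the 80% applies to that population. Statistical analyses, read as written, divides the same patients into two analyses of about half the size and does not mention the whole.

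An analyst following the text would therefore not run the comparison the trial was sized for, and would run two that it was not sized for. If the intervention truly gained 50 m in both subtypes, each subtype analysis could easily miss it, and the text does not say how the two results would answer the primary question.

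**Working it through.** **Inputs from the protocol article**
- Sample size: effect size d = 0.6, alpha 0.05, beta 0.2, 45 per arm, target difference 50 m.
- Sample size: walking distance "ranges from 242 m (standard deviation 71 m) up to 427 m (standard deviation 100 m"), so the SD lies between 71 m and 100 m.
- Sample size: 3.5 new heart failure patients per GP, half HF-REF and half HF-PEF; 26 GPs, plus 4 practices for clustering.
- Not given: the sidedness of the test, the ICC, and the correlation between baseline and 6-month walking distance. Values used for these below are assumptions.

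**Formula.** Power of a two-sample t-test with n per arm, from the noncentral t distribution with 2n − 2 degrees of freedom and noncentrality d × √(n/2), two-sided at 0.05.

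**Step 1: reproduce the plan's figure.** With n = 45 and d = 0.6, the noncentrality is 0.6 × √22.5 = 2.85 and power is 80.4%. At n = 44 it is 79.5%. So 45 per arm reproduces as a two-sided test. An effect size of 0.6 for 50 m implies an SD of 50/0.6 = 83.3 m. The GP count also fits: 26 × 3.5 = 91, about 2 × 45.

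**Step 2: apply the stated analysis.** Half of 45 is 22.5 per arm in each subtype. The noncentrality falls to 0.6 × √11.25 = 2.01, almost equal to the critical value of 2.02.

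| Patients per arm, one subtype | Power, d = 0.6 |
|---|---|
| 22 | 49.4% |
| 22.5 | 50.3% |
| 23 | 51.2% |

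Over the stated SD range, at 22.5 per arm:
- SD 100 m (d = 50/100 = 0.50): 37%
- SD 71 m (d = 50/71 = 0.70): 64%

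**Step 3: count the extra practices.** 30 × 3.5 = 105 patients, or 105/4 = 26.25 per arm per subtype. With 3.5/2 = 1.75 patients per GP in each subtype, the design effect is 1 + 0.75 × ICC.

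| Assumed ICC | Design effect | Effective n per arm | Power |
|---|---|---|---|
| 0 | 1 | 26.25 | 57% |
| 0.05 | 1.0375 | 25.3 | 55% |
| 0.10 | 1.075 | 24.4 | 54% |

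**Step 4: allow for baseline adjustment.** If ANCOVA includes baseline walking distance with correlation r, the effect size becomes 0.6/√(1 − r²).

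| Assumed r | Effect size | Power, 90 patients (no clustering) | Power, 105 patients (ICC 0.10 to 0) |
|---|---|---|---|
| 0.5 | 0.69 | 62% | 66% to 69% |
| 0.6 | 0.75 | 69% | 73% to 76% |
| 0.7 | 0.84 | 79% | 82% to 85% |

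**Step 5: size per subtype.** On the plan's basis, 80% power in each subtype needs 45 per arm in each, that is 4 × 45 = 180 patients before any allowance for clustering, against 90.

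**The case against.** The best defence is that the article condenses a fuller plan. Sample size names one primary comparison between the arms, and the Key objectives and Discussion pose the randomised question for heart failure patients overall. The sentence on separate analyses may have been meant as an addition to a pooled comparison. That is possible, but the sentence as printed replaces the pooled comparison rather than adding to it. Separate analysis also has a rationale: the Intervention section gives the two subtypes different treatment schemes, and the Background reports no significant benefit of the main drug classes in HF-PEF. That justifies reporting by subtype; it does not supply the power.

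It is also fair to say that 50% is not the power of the planned model, which is a multilevel ANCOVA. It is the power on the plan's unadjusted t-test basis. With 105 patients and an assumed correlation of 0.7, a subtype analysis would exceed 80%. This part of the objection stands, and any claim that adjusted power must stay below 80% would be wrong.

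A reader might go further than the documents allow in three ways.
- One might infer that no analysis in this trial is confirmatory. The article does name a primary outcome and implies a pooled comparison; it only fails to carry that comparison into the analysis section.
- One might infer two co-primary tests with a false-positive chance of 1 − 0.95² = 9.75%. The article never calls the subtype tests co-primary, that figure assumes independence, and an alpha rule may sit in an analysis plan that is not shown.
- One might call a null subtype result uninformative, or the GP-level variance barely estimable. A confidence interval still informs, and the documents give no basis for the claim about variance.

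**Conclusion.** The inconsistency stands and concerns the primary outcome: the 80% power belongs to a pooled comparison that the analysis section does not state. The size of the shortfall depends on the basis. It is largest on the plan's unadjusted basis, and it closes only if recruitment reaches the full 105 and baseline walking distance predicts the 6-month distance strongly. The subtype figures rest on the planned 50/50 mix and equal arms. Isolated right-sided heart failure, a third class under Outcome measures, falls in neither subtype analysis, so any such patients would reduce the subtype numbers further.

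**What to change.** Reconcile Sample size and Statistical analyses. The recommended wording names one primary analysis: a multilevel ANCOVA of 6-month walking distance in all trial patients with heart failure, with GP as the cluster and baseline walking distance and heart failure subtype as covariates. State whether patients with isolated right-sided heart failure belong to this population. Report HF-REF and HF-PEF as secondary estimates with confidence intervals, taken from an arm-by-subtype interaction in the same model.

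If the separate analyses are to remain primary, restate their power as about 50% each on the plan's basis, or give the correlation and ICC that support a higher figure. Also say how the two results jointly decide the trial.

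The first option changes wording only and needs no extra patients or data. Its price is that the subtype results become supportive.

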### Results of inclusion

Thirty GPs are included in the study, 14 were randomized to the care as usual arm and 16 to the intervention arm. We invited 1,527 elderly patients with shortness of breath on exertion to participate in the study. Of the invited patients, 77% responded, and eventually 38% was willing to participate. Reasons named for non-participation were; expected burden too high (40%), already known to a cardiologist (24%), other demanding health problems (15%), not experiencing shortness of breath anymore (12%), and severe immobility (5%).

Finally, 585 patients signed informed consent and were included in our study. The mean age of the participants was 74.1 (SD ±6.3) years. Stratified by age, 57% was aged between 65 and 74 years, 37% between 75 and 84 years, and 6% was aged 85 years or over. The percentage females was 54.5%. Important comorbidities were pulmonary disease (55.2%), hypertension (53%), hypercholesterolemia (32%), and ischemic heart disease (20%). The 14 GPs in the care as usual arm yielded 351 participants, and the 16 GPs of the up-titration arm 234 participants. Baseline characteristics of included patients divided between both groups are described in Table 1.

**Table 1 T1:** Baseline characteristics of the 585 participants, divided in the intervention and care as usual group

**Characteristics**	**All**	**Care as usual**	**Intervention***	
	**n = 585**	**n = 351 (60%)**	**n = 234 (40%)**	**p-value**
General				
Mean age in years ± sd	74.1 ± 6.3	73.8 ± 6.1	74.4 ± 6.5	0.25
Female sex	319 (54.5)	181 (51.6)	138 (59.0)	0.08
MRC dyspnea score ≥ 3	157 (26.8)	97 (27.6)	60 (25.6)	0.59
Cardiovascular comorbidities				
Ischemic heart disease	116 (19.8)	70 (19.9)	46 (19.7)	0.93
Prior myocardial infarction	43 (7.4)	27 (7.7)	16 (6.8)	0.70
Prior PCI/CABG	47 (8.0)	29 (8.3)	18 (7.7)	0.80
Vascular comorbidity	351 (60.0)	217 (61.8)	134 (57.3)	0.27
Hypertension	310 (53.0)	196 (55.8)	114 (48.7)	0.09
Hypercholesterolemia	187 (32)	115 (32.8)	72 (30.8)	0.61
Diabetes Mellitus	79 (13.5)	47 (13.4)	32 (13.7)	0.92
Prior stroke or TIA	51 (8.7)	27 (7.7)	24 (10.3)	0.28
Peripheral arterial disease	35 (6.0)	22 (6.3)	13 (5.6)	0.72
Atrial fibrillation	42 (7.2)	33 (9.4)	9 (3.8)	0.01
Non-cardiovascular comorbidities				
Cognitive disorders	110 (18.8)	50 (14.2)	60 (25.6)	0.001
Asthma/COPD	323 (55.2)	200 (57.0)	123 (52.6)	0.29
Depression	72 (12.3)	39 (11.1)	33 (14.1)	0.28
Medication				
Loop diuretics	55 (9.4)	36 (10.3)	19 (8.1)	0.39
Thiazide diuretics	147 (25.1)	89 (25.4)	58 (24.8)	0.88
ACE-inhibitors	120 (20.5)	70 (19.9)	50 (21.4)	0.68
ARBs	128 (21.9)	83 (23.6)	45 (19.2)	0.21
Beta-blockers	128 (21.9)	79 (22.5)	49 (20.9)	0.65
Digitalis	5 (0.9)	4 (1.1)	1 (0.4)	0.36
Aldosterone antagonists	7 (1.2)	7 (2.0)	0 (0.0)	0.03
Oral anticoagulants	51 (8.7)	37 (10.5)	14 (6.0)	0.06
Antiplatelets	147 (25.1)	84 (23.9)	63 (26.9)	0.41
Statins	179 (30.6)	110 (31.3)	69 (29.5)	0.63
Nitrates	41 (7.0)	26 (7.4)	15 (6.4)	0.64
Calcium channel blockers	76 (13.0)	54 (15.4)	22 (9.4)	0.04

Values are numbers (percentages).

*Intervention = a half-day training in the management of HF and the practical application of an up-titration scheme for HF-REF and HF-PEF.

Sd = standard deviation, MRC = medical research council, PCI = percutaneous coronary intervention, CABG = coronary artery bypass grafting, TIA = transient ischemic attack, COPD = chronic obstructive pulmonary disease, ACE = angiotensin converting enzyme, ARB = angiotensin receptor blocker, HF = heart failure, HF-REF = heart failure with reduced ejection fraction, HF-PEF = heart failure with preserved ejection fraction.

## Discussion

The diagnostic part of our study will provide information on the prevalence rate of previously unrecognized HF in older community-dwelling persons with shortness of breath on exertion. The cluster randomized comparison will reveal whether a single half-day training of GPs in the management of HF and the practical appliance of an up-titration scheme results in subsequent improvements in functionality, HRQoL, and uptake of HF medication compared to care as usual. In addition, cost-effectiveness will be examined. We expect that our diagnostic-therapeutic strategy is easy applicable and implementable, and above all, is able to detect a large number of patients with previously unrecognized HF in primary care and optimize their treatment, resulting in increased functional capacity and HRQoL.

### Regulation statement

This study is conducted according to the principles of the current version of the declaration of Helsinki and in accordance with the Dutch law on Medical Research Involving Human Subjects Act (WMO).

### Ethics committee approval

The study was approved by the medical ethical committee (METC) of the University Medical Center Utrecht, the Netherlands.

## Abbreviations

HF: Heart failure; HF-REF: Heart failure with reduced ejection fraction; ACE: Angiotensin converting enzyme; ARB: Angiotensin receptor blocker; HFPEF: Heart failure with preserved ejection fraction; GP: General practitioner; 6MWT: Six-minute walking test; HRQoL: Health-related quality of life; ECG: Electrocardiogram; NTproBNP: Amino-terminal pro-B-type natriuretic peptide; LVEF: Left ventricular ejection fraction; VAS: Visual analog scale; SF-36: Medical outcomes study 36-item short form health survey; EQ-5D: EuroQol; ANCOVA: Analysis of covariance.
